### Data Management

Data are being collected and managed in a custom-designed REDCap database. Data will be exported to the statistical analysis software, using relational logic checks to identify internal inconsistencies and out-of-range values. Systematic cleaning and verification of all collected data will be conducted to examine ranges, provenance, and missing values. Any inaccurate data points, outliers, and influential cases will be identified and corrected within REDCap. Dashboards and reports will be created and periodically updated to assist the team with recruitment and retention efforts, and track and minimize missing data.

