### Randomization

Computer-generated randomization assignment was done for all consented participants. We implemented a permuted block randomization with varying block sizes, blinded to the assessment team. Participants were randomized to four experimental conditions based on a 2 by 2 factorial design with equal probability allocation. The randomization list is concealed within the REDCap randomization module. We have programmed this such that the participant can be randomized and allocated only to an experimental condition after it is confirmed that baseline data have been collected and entered. Once the primary outcome measures are entered in REDCap, the study staff members can assign the participants to their respective experimental conditions. The statistician and the Principal Investigators are blinded, but the participants and the health coach are not blinded. All participants enrolled in the study were randomized to one of the four arms:

Arm 1: Adaptive reward+weekly automated coachingArm 2: Adaptive reward+weekly human coachingArm 3: Fixed reward+weekly automated coachingArm 4: Fixed reward+weekly human coaching

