### Sample Size Justification

The primary objective of this feasibility study is not to serve as a definitive, well-powered trial, but to conduct a pilot study that is sufficiently large to estimate design parameters, as well as assess feasibility parameters, such as attrition rate, adherence, and pre-post correlation [58-60]. Accounting for the bias and precision of the estimated pooled SD can help us conduct rigorous power and sample size calculations for a subsequent confirmatory study [61]. We are randomizing 88 participants across four conditions (22 per experimental condition). This is almost twice the number of participants per condition recommended when undertaking pilot studies, when there is no prior information on which to base a sample size [62]. The goal of our pilot study is also to estimate precise effect sizes and design parameter estimates, which requires sufficiently large pilot studies. Based on simulations published by Teare et al [61], an external pilot study should have at least 70 participants when estimating the pooled SD for a continuous outcome. Because we are using a factorial experiment, for each of the main effects, we will have 88 participants, with 44 participants in each of the two comparators. Hence, we have a sufficiently large pilot study to detect precise estimates of effect sizes for the two main effects and other design parameter estimates, such as pre-post correlation.

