We also present power calculations of our experiment based on our sample size of 88. Assuming a type 1 error rate of 0.05, a conservative pre-post correlation of 0.5 in ANCOVA, and an attrition rate of 15%, we will have 80% power to detect an effect size (Cohen *d*) of 0.572 in our primary outcome. This would imply a main effect difference of 0.86% units of HbA_1c_, assuming an SD of 1.5% [63]. Even if we assume the pre-post correlation is 0.3, which is very conservative, we will have 80% power to detect an effect size of 0.63 for the main effect. Assuming a more realistic pre-post correlation of 0.7, we can detect an effect size of 0.472. Missing outcomes data will be imputed using maximum likelihood estimation or a multiple imputation procedure, and primary analyses will not be restricted to only completers. Hence, our proposed study sample size of 88 participants is powered to detect an even smaller effect size than suggested here since the effective sample size, even assuming an attrition of 15%, would be between 74 and 88. Thus, our pilot study is well-powered to detect moderate to medium effect sizes. These power calculations were done using the MOST package in R (R Core Team), developed by Dziak et al [64].

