#### Analytic Strategy for Preliminary Effectiveness Analyses

We will also estimate effect sizes as preliminary effectiveness estimates. All statistical analyses will follow an intent-to-treat approach. In line with a pilot study, we will also report 75% and 85% CI estimates in addition to the traditional 95% CIs to further aid in the statistical interpretation of the findings [65]. We will use linear mixed models to estimate effects by accounting for correlated data and benefit from the maximum likelihood estimation procedure that uses all information in the dataset in the presence of missing outcome data. Our overall approach will be similar to Pellegrini et al [38]. To evaluate the main effect of each component on pre-post differences in outcomes, we will use baseline as the reference cell to determine differences in change across time (ie, 6 months vs baseline) [38]. However, these effects will be statistically modeled as component-by-time interactions, with the 6-month outcome as the primary end point. We will also include two-way interactions between components (eg, Factor 1 by Factor 2 by time interaction). We will then identify all the active components or combinations of components, where active is operationalized as a mean reduction of 0.5 units (%) in HbA_1c_ between baseline and month 6 [66,67]. Similar analyses will be done for secondary outcomes. Where information related to minimally clinically important differences is available, we will use it to assess whether the combination is active. For example, an average 5% weight loss is considered to be active in the case of weight. We will leverage the generalized linear modeling framework and resampling-based approaches for nonnormal outcomes. We will conduct exploratory analyses to assess biases in the self-reported PROs. While we are not statistically powered to do mediation or moderation analyses, in line with the MOST Preparatory Phase, we will conduct exploratory mediation and moderator analyses using our tracking data as potential mediators or moderators.

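### The data-management rule lets valid outliers and influential cases be changed in REDCap; it should limit correction to values shown to be wrong against source

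*Protocol article*

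**What the plan says.** The Data Management section of the protocol article first describes logic checks for inconsistent and out-of-range values. It continues: "Systematic cleaning and verification of all collected data will be conducted to examine ranges, provenance, and missing values". The next sentence is the rule at issue: "Any inaccurate data points, outliers, and influential cases will be identified and corrected within REDCap".

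Three other places bear on it:

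- Randomization, on blinding: "The statistician and the Principal Investigators are blinded, but the participants and the health coach are not blinded".
- Sample Size Justification, on the purpose of the pilot, which is to be "sufficiently large to estimate design parameters, as well as assess feasibility parameters, such as attrition rate, adherence, and pre-post correlation". The same section also names the pooled SD and the effect sizes as targets.
- Analytic Strategy for Preliminary Effectiveness Analyses, which provides generalized linear models and resampling for outcomes that are not normally distributed.

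The article gives no criterion for an outlier or an influential case, and does not say what correcting one would consist of.

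**The concern.** The sentence applies one action to three different things. An inaccurate value is wrong, and can be put right against the laboratory report, the survey form or the call record. An outlier is only unusual and may be a true result. An influential case is defined by how far it moves a fitted estimate; nothing in that definition makes it wrong, and there may be no source error to correct.

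Because the last two are listed beside inaccurate values, and not as signals that a value may be inaccurate, someone following the text could change a verified HbA1c or weight in the study database. Removing real extremes makes the data look less variable and the month-6 values look more predictable from baseline. Those two quantities size the confirmatory trial, so the error would be carried forward.

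**Working it through.** **1. The plan's own figure reproduces.** Inputs from Sample Size Justification: 88 participants, 44 per level of each factor, 15% attrition, type 1 error 0.05 (taken as two-sided), correlation 0.5, Cohen d 0.572, SD 1.5%.

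- Completers: 88 × 0.85 = 74.8, taken as 74, or 37 per level.
- ANCOVA scales the SD by √(1 − 0.5²) = 0.866.
- Noncentrality: (0.572 / 0.866) × √(37/2) = 2.84. Power from the noncentral t is 0.800, as stated.
- 0.572 × 1.5 = 0.858, the stated 0.86% HbA1c.

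No printed figure is wrong. The calculation does show that the required sample size depends on SD² × (1 − ρ²), the squared residual SD.

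**2. What changing valid influential values does.** The assumptions are mine, because the article gives no rule:

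- N = 74, SD 1.5, correlation 0.5, no true effect, and every value valid.
- A case is flagged when Cook's distance exceeds 4/N, from an ANCOVA that includes arm. About 4 of 74 valid records are flagged.
- Flagged month-6 values are either pulled in to 1.5 residual SDs or replaced by the fitted value. There were 20,000 runs per row.

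| Normal data | Residual SD | Pre-post correlation | Type I error | 95% CI coverage |
|---|---|---|---|---|
| Values left alone | 1.294 | 0.496 | 0.051 | 0.949 |
| Pulled in | 1.208 | 0.523 | 0.071 | 0.929 |
| Replaced by fitted value | 1.117 | 0.549 | 0.120 | 0.880 |

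The fall in residual SD is 1 − 1.208/1.294 = 6.6% and 1 − 1.117/1.294 = 13.7%. Across N = 74 and N = 88, with or without arm in the flagging model, the ranges are about 6-14% for the residual SD and about 0.51-0.55 for the correlation.

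**3. What depends on arm.** Mean bias in the main effect is about zero in these runs. Type I error rises (to about 0.06-0.13) only when arm is in the model used for flagging. With arm left out it stays close to 0.05 (0.044 in one run of 5,000 with fitted-value replacement). The loss of variance and the raised correlation remain either way.

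**4. Heavier tails.** With t-distributed data on 5 degrees of freedom, and arm in the flagging model, the residual SD falls from 1.287 to 1.111 or 1.006 (13.7% or 21.8%). The correlation becomes 0.549 or 0.586.

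**5. Consequence for the next trial.** A residual SD understated by 6 to 14% multiplies the calculated sample size by 0.94² = 0.88 to 0.86² = 0.74, which is 12 to 26% too few participants. The residual SD already includes the change in correlation, so the two effects must not be added.

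**6. One value.** Suppose a genuine month-6 HbA1c of 12% were replaced by an assumed level mean of 7.5%. With 44 per level the mean moves by 4.5/44 = 0.10%; with 37 per level, by 4.5/37 = 0.12%. Against the 0.5% reduction that the plan uses to call a component active, that is about 20% or 24%. The Results section reports 6-month follow-up complete for all 88, so 44 is the better divisor.

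**The case against.** The strongest reply is that the sentence belongs to a data-cleaning paragraph and follows checks of range and provenance. Read that way, flagged values are queried and errors are fixed, and a verified value leaves nothing to correct. That may well be the intent. But the sentence does not say it, and influential cases fit that reading poorly.

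A reader might infer something stronger: that data will be altered after the results are seen, in a direction the analyst can choose, with no unaltered dataset left. The article does not support this.

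- It does not say when influence is assessed relative to the outcome analysis.
- The statistician and Principal Investigators are blinded, which limits editing by arm. The article does not say who makes the corrections.
- It does not say that originals are discarded. For the monitoring calls, the Intervention Components section says that raw recordings and transcriptions are stored.
- No systematic bias in the main effects appears in the check above.

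Nor is there a conflict with the intent-to-treat statement, "All statistical analyses will follow an intent-to-treat approach". That principle governs who is analysed and in which arm, not how individual values are cleaned.

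It is also fair that audit trail, database lock and outlier criteria usually sit in a data-management plan or SAP. Their absence from an article is no fault. What remains is the wording the article does contain, which permits too much.

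**Conclusion.** The point holds as a wording fault with a real statistical consequence if the rule is followed literally. Valid extremes could be changed in the study database. In the normal-data illustration this understates the residual SD by about 6 to 14%, raises a correlation of 0.50 to about 0.51-0.55, and makes confidence intervals too narrow when flagging uses arm. These sizes rest on an assumed Cook's distance cut-off and assumed replacement rules. They show what could happen, not what will.

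Severity is moderate. Blinding limits arm-directed editing. The Outcomes section makes feasibility primary and HbA1c secondary, and recruitment and retention counts are little affected. The point matters because estimating the SD, correlation and effect sizes for the next trial is a stated purpose of this one.

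**What to change.** Replace the sentence in Data Management with:

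> Flagged values are checked against source; only values shown to be wrong are corrected in REDCap. Verified outliers and influential cases stay as recorded in the main analysis, and their influence is examined only in a sensitivity analysis.

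The sensitivity analysis can be a robust or rank-based fit, or a fit with and without the cases. Because the Results section reports follow-up complete and analysis under way, the report should also state whether any verified value was changed and, if so, restore it for the main analysis.

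The cost is a short rewording and one small extra analysis. Nothing is lost for skewed outcomes, since the plan already provides methods for them.

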### Sample Size Justification

The primary objective of this feasibility study is not to serve as a definitive, well-powered trial, but to conduct a pilot study that is sufficiently large to estimate design parameters, as well as assess feasibility parameters, such as attrition rate, adherence, and pre-post correlation [58-60]. Accounting for the bias and precision of the estimated pooled SD can help us conduct rigorous power and sample size calculations for a subsequent confirmatory study [61]. We are randomizing 88 participants across four conditions (22 per experimental condition). This is almost twice the number of participants per condition recommended when undertaking pilot studies, when there is no prior information on which to base a sample size [62]. The goal of our pilot study is also to estimate precise effect sizes and design parameter estimates, which requires sufficiently large pilot studies. Based on simulations published by Teare et al [61], an external pilot study should have at least 70 participants when estimating the pooled SD for a continuous outcome. Because we are using a factorial experiment, for each of the main effects, we will have 88 participants, with 44 participants in each of the two comparators. Hence, we have a sufficiently large pilot study to detect precise estimates of effect sizes for the two main effects and other design parameter estimates, such as pre-post correlation.

We also present power calculations of our experiment based on our sample size of 88. Assuming a type 1 error rate of 0.05, a conservative pre-post correlation of 0.5 in ANCOVA, and an attrition rate of 15%, we will have 80% power to detect an effect size (Cohen *d*) of 0.572 in our primary outcome. This would imply a main effect difference of 0.86% units of HbA_1c_, assuming an SD of 1.5% [63]. Even if we assume the pre-post correlation is 0.3, which is very conservative, we will have 80% power to detect an effect size of 0.63 for the main effect. Assuming a more realistic pre-post correlation of 0.7, we can detect an effect size of 0.472. Missing outcomes data will be imputed using maximum likelihood estimation or a multiple imputation procedure, and primary analyses will not be restricted to only completers. Hence, our proposed study sample size of 88 participants is powered to detect an even smaller effect size than suggested here since the effective sample size, even assuming an attrition of 15%, would be between 74 and 88. Thus, our pilot study is well-powered to detect moderate to medium effect sizes. These power calculations were done using the MOST package in R (R Core Team), developed by Dziak et al [64].

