### Statistical Analyses

#### Feasibility-Related Analyses

Descriptive statistics of feasibility measures such as adherence, dropouts, and recruitment will be estimated and provided. Bias-corrected bootstrap CIs of the Spearman correlation between baseline and 6-month assessment will be reported. For participants identified through the i2b2 system at UAB Health System, we are tracking the following: (1) no response, (2) screened but failed, (3) screened as eligible but did not consent, (4) screened as eligible and consented, (5) enrolled but withdrew before the intervention started, (6) started the intervention but withdrew during the study, and (7) completed the intervention and final data collection. In addition to the descriptive measures of recruitment outcomes, we will run at least a binary logistic regression model to explore and predict factors associated with successful recruitment outcomes. Successful recruitment will be defined as participants screened as eligible, consented to participate, completed the intervention, and completed the final data collection. Age, gender, race, location status (urban vs nonurban), and health insurance status will be covariates.

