## Discussion

### Principal Findings

This paper sought to outline the study protocol used in a pilot study grounded in SCT, aiming to assess the feasibility of an AI-assisted, low-cost, lifestyle modification intervention for glycemic control in the Deep South. The intervention is designed to be accessible through a standard telephone service and leverages MOST, an efficient and rigorous resource-management and continuous-improvement framework. The MOST design allows us to explore (1) a fixed versus adaptive (gamified) rewards program, and (2) automated versus human-delivered weekly health coaching for four total experimental conditions to see which is most effective for T2DM management. Findings from this pilot and feasibility study will inform the resources needed for a well-powered optimization trial. We will estimate key design parameters—such as effect sizes and pre-post correlations—to guide future sample size calculations. The study also helps identify protocol modifications to improve scalability, recruitment, and participant-centeredness.

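### The guideline cited for precise main-effect estimates concerns the SD; by the plan's own inputs the 95% CI for HbA1c is about ±0.45 to ±0.66 percentage points, so the observed effect should not size the next trial

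*Protocol article*

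**What the plan says.** Three parts of the Protocol article bear on this.

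- **Sample Size Justification.** The section opens by saying that the study is not intended as a definitive, well-powered trial. It then makes precise effect sizes a goal, cites a simulation-based guideline of at least 70 participants for the pooled SD of a continuous outcome, notes 44 participants per level of each factor, and concludes that "we have a sufficiently large pilot study to detect precise estimates of effect sizes for the two main effects". Next comes a power calculation with type 1 error 0.05, pre-post correlation 0.5 and 15% attrition: "we will have 80% power to detect an effect size (Cohen *d*) of 0.572 in our primary outcome". This is translated to 0.86% HbA1c at an SD of 1.5%. The detectable d is 0.63 at a correlation of 0.3, called very conservative, and 0.472 at 0.7, called more realistic. The section ends: "our pilot study is well-powered to detect moderate to medium effect sizes".
- **Analytic Strategy for Preliminary Effectiveness Analyses.** Effects are modelled as component-by-time interactions. Components or combinations count as active at a mean HbA1c reduction of 0.5% from baseline to month 6. CIs at 75%, 85% and 95% will be reported.
- **Principal Findings (Discussion).** Effect sizes and pre-post correlations will be estimated "to guide future sample size calculations".

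**The concern.** A sample that estimates an SD adequately can still estimate a difference between means poorly. The step from the 70-participant guideline to precise main effects is therefore unsupported, and the article gives no expected CI width that would let a reader judge it. The closing power statement also sits badly with the section's opening disclaimer.

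What is at stake is the next step. If the observed effect is taken to be precise and becomes a planning value, its sampling error passes into the size of the optimization trial. A component could also be kept or dropped on an estimate whose interval covers both no effect and twice the threshold.

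**Working it through.** **Inputs, all from the article.** SD 1.5% HbA1c; correlation r = 0.3, 0.5 or 0.7; 88 randomized, 44 per factor level; effective N between 74 (15% attrition) and 88; type 1 error 0.05, taken as two-sided because that reproduces the stated figures; threshold 0.5%.

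**1. The plan's own figures.** ANCOVA main effect with N analysed in two equal groups, noncentral t with N − 5 degrees of freedom and noncentrality d × √N / (2 × √(1 − r²)).

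- r = 0.5, N = 74: 0.572 × 8.602 / (2 × 0.866) = 2.84, power 80.0%
- r = 0.3, N = 74: d = 0.63, power 80.0%
- r = 0.7, N = 74: d = 0.472, power 80.0%
- 0.572 × 1.5 = 0.858, the stated 0.86%

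All stated figures reproduce. The arithmetic is sound.

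**2. Expected precision from the same inputs.** SE = 1.5 × 2 × √(1 − r²) / √N; 95% half-width = t(0.975, N − 5) × SE. For r = 0.5 and N = 74: SE = 3 × 0.866 / 8.602 = 0.302, and 1.995 × 0.302 = 0.603.

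| r | N = 74 | N = 88 |
|---|---|---|
| 0.3 | ±0.66 | ±0.61 |
| 0.5 | ±0.60 | ±0.55 |
| 0.7 | ±0.50 (0.497) | ±0.45 (0.454) |

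Units are percentage points of HbA1c. In the r = 0.5, N = 74 case the half-width is 0.40 in d units (0.603 / 1.5), the 75% CI is ±0.35 and the 85% CI is ±0.44. An observed effect of exactly 0.5% would have a 95% CI of about −0.1% to 1.1%.

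**3. Power for a 0.5% between-level difference** (d = 0.5 / 1.5 = 0.333), same formula as step 1.

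| r | N = 74 | N = 88 |
|---|---|---|
| 0.3 | 32% | 37% |
| 0.5 | 37% | 43% |
| 0.7 | 51% | 58% |

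The stated detectable difference is 0.86 / 0.5 = 1.7 times this threshold.

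**4. Power at a medium effect, d = 0.5.**

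| r | N = 74 | N = 88 |
|---|---|---|
| 0.3 | 60% | 68% |
| 0.5 | 69% | 76% |
| 0.7 | 84% | 90% |

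**5. Illustration, only if the point estimate were used directly for planning.** Suppose the true effect is 0.5% and the pilot estimate lies one SE away (r = 0.5, N = 74): 0.5 − 0.302 = 0.198 or 0.5 + 0.302 = 0.802. Required size scales with the inverse square of the effect, so the next trial would come out at (0.5 / 0.198)² = 6.4 or (0.5 / 0.802)² = 0.39 times the right size.

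**The case against.** Several points on the other side stand.

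- **Correlation and N.** It is tempting to say flatly that the CI half-width exceeds the 0.5% threshold. That is true at r = 0.3 and 0.5, but at the article's more realistic r = 0.7 it is 0.497 or 0.454. The Results section reports that the 88 randomized participants completed follow-up, so the N = 88 column may be the relevant one.
- **Power claim.** A reader might infer that the claim about moderate to medium effects is simply false. At r = 0.7, power at d = 0.5 is 84% to 90%, so the claim holds there. It fails the usual 80% at r = 0.3 and 0.5.
- **Threshold.** A reader might infer that the design is underpowered for the effect the plan cares about. The 0.5% rule is worded as a mean reduction from baseline to month 6 and could be a within-group change. Setting it against a main effect follows the component-by-time model but is a reading. For a within-group change, the approximate half-width is 1.96 × 1.5 × √(2(1 − r)) / √n. At r = 0.5 this is 0.48 per factor level (n = 37) and 0.68 per cell (n = 18.5).
- **Context.** Feasibility is primary, the effects are called preliminary, and lower-level CIs are planned. Nothing in the text says that a null result would be read as no effect.
- **Planning use.** The Discussion says effect sizes will guide calculations, not that a point estimate alone will set the size. The range in step 5 is therefore conditional.

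Two further criticisms do not hold. Reporting a Spearman correlation rather than Pearson is immaterial under normality (0.483 against 0.5). The absence of the pooled SD from the listed analyses is detail that an article may leave to the full plan.

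None of this supports the step from an SD guideline to precise effect sizes.

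**Conclusion.** The concern holds in limited form. No figure is miscalculated; the fault lies in what is concluded from the figures. The precision claim rests on a criterion for a different quantity. Across the article's own correlations and both N, the full 95% interval for a main effect on HbA1c is about 0.9 to 1.3 percentage points wide. Power for a 0.5% between-level difference never exceeds 58%, if the threshold is read that way. The well-powered statement depends on the correlation and needs reconciling with the disclaimer that opens the same section.

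These results rest on the article's SD of 1.5%, equal allocation, a two-sided 5% test and ANCOVA-type variance reduction. Using the pilot to estimate SD, pre-post correlation, attrition and adherence is unaffected; only the observed effect as a planning value is in question.

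**What to change.** - **Sample Size Justification:** remove the claim of precision for effect sizes, and confine the 70-participant guideline to the SD. Replace the well-powered sentence with the detectable effects by correlation (0.63, 0.572, 0.472). Add the expected 95% CI half-width and the power for 0.5%, by correlation and for N = 74 and 88, as tabulated above.
- **Analytic Strategy:** say whether the 0.5% rule is a between-level difference or a within-group change, so that the power figure refers to a defined quantity.
- **Principal Findings:** state that the optimization trial will be sized on a prespecified clinically relevant difference, with SD, pre-post correlation, attrition and adherence taken from the pilot. Report the pilot effects with their CIs, not as the planning input.

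The cost is a few sentences and one small table. No new data or change of design is needed, though the stated properties will look less favourable.
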